## Abstract

**Introduction:**

In recent years, an unprecedented emphasis has been given to the control of neglected tropical diseases, including soil-transmitted helminths (STHs). The mainstay of STH control is school-based deworming (SBD), but mathematical modelling has shown that in all but very low transmission settings, SBD is unlikely to interrupt transmission, and that new treatment strategies are required. This study seeks to answer the question: is it possible to interrupt the transmission of STH, and, if so, what is the most cost-effective treatment strategy and delivery system to achieve this goal?

**Methods and analysis:**

Two cluster randomised trials are being implemented in contrasting settings in Kenya. The interventions are annual mass anthelmintic treatment delivered to preschool- and school-aged children, as part of a national SBD programme, or to entire communities, delivered by community health workers. Allocation to study group is by cluster, using predefined units used in public health provision—termed community units (CUs). CUs are randomised to one of three groups: receiving either (1) annual SBD; (2) annual community-based deworming (CBD); or (3) biannual CBD. The primary outcome measure is the prevalence of hookworm infection, assessed by four cross-sectional surveys. Secondary outcomes are prevalence of *Ascaris lumbricoides* and *Trichuris trichiura*, intensity of species infections and treatment coverage. Costs and cost-effectiveness will be evaluated. Among a random subsample of participants, worm burden and proportion of unfertilised eggs will be assessed longitudinally. A nested process evaluation, using semistructured interviews, focus group discussions and a stakeholder analysis, will investigate the community acceptability, feasibility and scale-up of each delivery system.

**Ethics and dissemination:**

Study protocols have been reviewed and approved by the ethics committees of the Kenya Medical Research Institute and National Ethics Review Committee, and London School of Hygiene and Tropical Medicine. The study has a dedicated web site.

**Trial registration number:**

NCT02397772.

Strengths and limitations of this studyThe study has a strong design incorporating random allocation, blinding of assessors to the primary outcome, and builds on and will, subsequently, refine mathematical modelling.The interventions include alternative treatment strategies using two different delivery systems, and are well-established, of long duration (24 months) and nested within an ongoing national control programme.The study includes cost-effectiveness analysis and analysis of community acceptability, feasibility and scale-up of each delivery system.A limitation of the study is its reliance on existing health structures to implement the intervention.The study will contribute to evidence regarding the cost-effectiveness of soil-transmitted helminth control and thereby inform national and global policy.

## Introduction

Neglected tropical diseases (NTDs) are a cluster of tropical diseases that affect more than one billion people worldwide, mainly among poor populations living at the periphery of health systems.^1^ NTDs can cause disability, disfigurement, undernutrition and cognitive impairment, yet many NTDs can be easily controlled by periodic mass treatment using safe and broad spectrum drugs. Global efforts to control NTDs reached a turning point in 2012, when WHO launched its NTD Roadmap,^1^ and partners met in London, and pledged to work together to control and eliminate 10 NTDs by 2020.^2^ As part of this commitment, pharmaceutical companies pledged to donate the drugs required for mass treatment programmes and the challenge now is to support countries in developing sustainable systems to distribute donated medicines.

According to the 2010 Global Burden of Disease study,^2^ the soil-transmitted helminths (STHs) spp *Ascaris lumbricoides*, *Trichuris trichiura* and hookworm, contribute the greatest disease burden among the NTDs, causing an estimated 4.98 million years lived with disability each year.^3^ Fortunately, much of this burden can be readily averted by periodic, population-based chemotherapy (also known as deworming). The WHO identifies three priority groups for deworming: school-age children, preschool-age children and women of childbearing age,^4^ as they typically harbour chronic and intense infections at a time when they are undergoing physical and/or cognitive development. An effective mechanism to reach school-age children is provided by school-based deworming programmes, which have been shown to cost-effectively reduce their STH-related morbidity.^5^
^6^ In 2013, some 237 million school-age children—equivalent to 39% of the global at-risk school-aged population—benefitted from STH treatment.^7^ However, if the 2020 target of treating 75% of school-age children is to be reached, there needs to be a concerted effort to scale-up deworming. Responding to this need, a new consortium was established in Paris in 2014, to assist countries to develop mechanisms for addressing STH among preschool-age and school-age children.^8^ Partners at the Paris meeting also committed support for evaluating the potential of interrupting the transmission of STHs using new tools and strategies. Recent analyses based on mathematical models of parasite transmission and the impact of treatment have suggested that the transmission of STHs can be interrupted (a breakpoint in transmission is crossed where parasite elimination is achieved) if treatment is expanded to adults and provided more frequently.^9–11^ While such models can provide new insights, there is an obvious need to test the predictions of the impact and cost-effectiveness of alternative treatment strategies through rigorous field studies.

If there is to be a move towards broadening the range of age groups targeted by STH treatment programmes, then it is necessary to identify suitable delivery systems. Possibly the longest running community-based NTD control programme that treats across all age groups is the African Programme for Onchocerciasis Control, which has helped countries create a community-directed treatment strategy by involving community-directed drug distributors and extending and strengthening health systems.^12–14^ A community-based approach is also employed by national lymphatic filariasis (LF) control programmes, whereby community drug distributors or community health workers (CHWs) provide community-wide delivery of albendazole plus ivermectin (or diethylcarbamazine in areas not endemic for onchocerciasis) to entire populations aged 2** **years and above.^15^ Although CHWs are increasingly used to promote healthy behaviours and deliver basic health services, especially in poor and underserved communities,^16^
^17^ the benefits of using a CHW-based approach for STH control is poorly understood at present.

This paper describes two cluster randomised trials in Kenya that seek to provide new evidence on the impact and cost-effectiveness of alternative treatment strategies and delivery systems in reducing the transmission of STHs. Such evidence will help establish proof-of-concept of the possibility of interrupting STH transmission and would likely be of value to policymakers in STH-endemic countries, and partners and funders supporting STH control.

### Aims and objectives

The overall aim of the trials is to evaluate the impact and cost-effectiveness of school-based versus community-based deworming on measures of STH transmission in Kenya. Specifically, we will test the hypothesis that treatment needs to be provided to a broad range of ages and/or at more frequent intervals than 1 year in order to interrupt the transmission of STH. The study also includes process and economic evaluations to assess the feasibility and implementation of the alternative treatment strategies and delivery systems, which will guide scale-up of the programmes in Kenya and other settings in Africa. The more detailed study objectives are:
To quantify the impact of school-based versus community-based mass treatment (treatment strategies and delivery systems) at annual and biannual intervals (treatment strategies) in reducing the transmission of STH spp, hookworm, *A. lumbricoides* and *T. trichiura*.To evaluate the costs and cost-effectiveness of alternative STH treatment strategies and delivery systems in reducing transmission.To assess the extent to which community-based treatment programmes for STH are acceptable to the community, which are feasible, given the health system capacity, and can be easily scaled-up across Kenya and elsewhere.

## Methods and analysis

Reporting of the study protocol has been verified in accordance with the SPIRIT (Standard Protocol Items for Randomised Trials) recommendations.

### Overall study design

Two paired community cluster randomised trials in different settings in Kenya will evaluate the impact and cost-effectiveness of annual school-based deworming, annual community-based deworming and biannual community-based deworming. The trials are designed as cluster randomised, open-label trials with three study groups. The primary outcome is the prevalence of hookworm. This outcome was selected because it is the STH spp that contributes most to morbidity, is responsible for the most DALYs lost due to STH^3^ and is the species most difficult to control using school-based deworming alone.^9^ Allocation to study group is by cluster, using predefined units used in public health provision—termed community units (CUs). The three study groups are:
*Control group*: Annual school-based deworming. Preschool and school children (typically aged 2–14 years) will receive a single dose of albendazole (400 mg) from trained school teachers, as part of the ongoing national school-based deworming programme.*Expanded age range group*: Standard school-based deworming supplemented by annual community-based deworming (2–99 years). All household members who are not enrolled in school will receive a single dose of albendazole (400 mg) from trained CHWs—known in Kenya as community health volunteers (CHVs).*Expanded age range and frequency group*: Annual school-based deworming supplemented by community-based deworming (2–99 years), followed by an additional community-based deworming 6 months later. All household members who are not enrolled in school will receive a single dose of albendazole (400 mg) from trained CHVs.

Mathematical models suggest that there is little difference in the impact of annual or biannual school-based deworming, given the expected prevalence in our study sites,^10^
^18^ and therefore we did not include biannual school-based deworming as a study group. In other settings where *A. lumbricoides* is more common and hookworm is absent, biannual treatment may be desirable due to the relatively higher levels of infection in school-age children compared to adults.

The primary outcome, the prevalence of hookworm infection, will be measured through cross-sectional parasitological surveys conducted at baseline and at 12, 24 and 30 months follow-up. The timing of the final follow-up survey takes into account differences in time since treatment of the annual and biannual treatment groups at 24 months. The overall study design is summarised in figure 1. A subsample of individuals from two CUs in each of the study groups will be followed longitudinally for two and half years, in order to better understand the transmission dynamics of STHs and to estimate key parameters for the mathematical models of transmission dynamics and treatment impact. A nested process evaluation, using semi-structured interviews, focus group discussions (FGDs) and a stakeholder analysis, will investigate the community acceptability, feasibility, given the local and regional health system structures and processes, and scale-up of the interventions.

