### Interventions

All study groups will receive treatment with albendazole (400 mg), which is highly efficacious against *A. lumbricoides* and hookworm, but has lower efficacy against *T. trichiura.*^19^ What differs between the three study groups is the age range of populations that receive treatment and the frequency at which treatment is provided.

School-based deworming will be implemented in all communities as part of the national school-based deworming programme (NSBDP). Launched jointly in 2009 by the Ministry of Education, Science and Technology (MoEST), and the Ministry of Health (MoH), and funded by the Children's Investment Fund Foundation, the programme's goal is to eliminate STHs and schistosomiasis as a national public health problem. A single 400 mg dose of albendazole is provided annually by trained teachers on designated deworming days. The programme targets all children in at-risk subcounties enrolled in public and private primary schools and early childhood development centres (kindergartens).^20^ Non-enrolled school-age children are also encouraged to come to school for treatment on deworming day. The NSBDP makes use of a cascade model whereby trainings, materials, drugs and funds are channelled from the national level through the county to the school level, involving officials from MoEST and MoH throughout the cascade. The emphasis is on MoEST for delivery and MoH for supervision. Treatment coverage data and remaining drugs are returned along the reverse cascade. No adaptations shall be made to the NSBDP for the study other than modification of the treatment and coverage forms to strengthen the data capture on treatment at the individual level, and to validate treatment coverage.

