Community-based deworming will be provided by CHWs, called CHVs in Kenya. CHVs already promote care seeking and compliance to antiretroviral and tuberculosis treatment, and mobilise populations during national health campaigns, as part of the national community health strategy.^21^ This strategy also includes the establishment of CUs, which each serve approximately 1000 households or 5000 people, with a single CHV providing service to approximately 100 households. For every 25 CHVs, there is one Community Health Extension Worker (CHEW) who is a Ministry of Health employee with training in public health or nursing. This CHEW provides supervision and technical support to the CHVs. The community health strategy was revised in 2010, with new guidance on the contents of CHV kits to include basic drugs such as paracetamol, albendazole and tetracycline.^22^ The community-based deworming in the present trials will provide door-to-door treatment, drawing on the previous experience of the National Programme for Elimination of LF, which, to date, has implemented four rounds of mass treatment (2002, 2005, 2008 and 2011), but with variable levels of treatment coverage.^23^

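### In both community groups, health volunteers treat only people not enrolled in school, yet the school programme targets only primary schools and kindergartens, so secondary pupils have no scheduled dose

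*Protocol article*

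**What the plan says.** The section Overall study design defines the annual community group as "Standard school-based deworming supplemented by annual community-based deworming (2–99 years"), with CHV treatment for household members who are not in school. The biannual group has the same annual package, "followed by an additional community-based deworming 6 months later. All household members who are not enrolled in school will receive a single dose". Neither definition says which level of school is meant.

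The Interventions section describes the other channel: "The programme targets all children in at-risk subcounties enrolled in public and private primary schools and early childhood development centres (kindergartens"). It adds: "Non-enrolled school-age children are also encouraged to come to school for treatment on deworming day". It also says that the trial changes nothing in the national programme except its treatment and coverage forms, so the trial does not widen the programme's reach.

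The Abstract summarises the interventions as treatment of preschool and school children within the national programme, "or to entire communities, delivered by community health workers".

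**The concern.** The community groups are built from two channels that should together reach everyone aged 2 to 99. As worded, they do not. The CHV rule excludes anyone enrolled in any school, while the school programme targets only some schools. A pupil in secondary school falls between them.

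This bears on the question the trial asks, which is whether "treatment needs to be provided to a broad range of ages and/or at more frequent intervals than 1 year" to interrupt transmission. An adolescent group left out of the expanded-age groups weakens the contrast under test. Nothing in the survey eligibility criteria removes secondary pupils: they require 12 months' residence and consent, and they provide for assent at ages 13–17. The primary outcome counts all sampled individuals, so these pupils can contribute to measured prevalence while having no scheduled dose. They could also keep contributing to transmission in their communities.

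**Working it through.** **The two rules side by side, for the community groups**

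| Resident | School programme | CHV round | Scheduled route to a dose |
|---|---|---|---|
| Primary or kindergarten pupil | targeted | not eligible (enrolled) | yes |
| School-age child, not enrolled | encouraged to attend | eligible | yes |
| Adult, not enrolled | not targeted | eligible | yes |
| Secondary pupil | not targeted | not eligible (enrolled) | none |

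The article never mentions secondary school, and no other section closes the gap. The only other way to a dose is treatment of survey participants found infected (Outcomes). That is not part of the intervention, and each survey samples only 225 of roughly 5000 people in a community unit.

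**Size**

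The plan gives no figure on this point to reproduce. The 40 clusters per group are not in dispute, and the predicted difference behind them appears only in Figure 3, which is not shown.

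Inputs from the documents:
- Coverage of 80% for school-based and 70% for community-based treatment (Figure 3 caption).
- Community units, "which each serve approximately 1000 households or 5000 people" (Interventions).
- 225 people surveyed per unit (Randomisation).

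Assumptions, not in the documents (Table 1 reports primary attendance but nothing on secondary enrolment):
- f, the share of residents in secondary school: 3–8%.
- s, the share in primary school or kindergarten: 20–40%.

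Formulas for coverage of residents at the annual round:
- As written: 0.80s + 0.70(1 − s − f)
- With secondary pupils eligible: 0.80s + 0.70(1 − s)
- Difference: 0.70f, so s drops out

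| s | f | As written | Secondary pupils eligible | Difference (points) |
|---|---|---|---|---|
| 20% | 3% | 69.9% | 72.0% | 2.1 |
| 30% | 5% | 69.5% | 73.0% | 3.5 |
| 40% | 8% | 68.4% | 74.0% | 5.6 |

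Per community unit of 5000:
- Secondary pupils: 5000 × 0.03 = 150 to 5000 × 0.08 = 400.
- Doses not scheduled per community round: 0.70 × 150 = 105 to 0.70 × 400 = 280.
- Expected number among 225 surveyed: 225 × 0.03 ≈ 7 to 225 × 0.08 = 18.

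**The case against.** The strongest reply is that context narrows the word school. The control group, defined just before, consists of preschool and school children typically aged 2–14 treated by teachers in the national programme, and the community groups supplement that programme. On that reading, people not in school are simply those outside the schools just described. Door-to-door delivery and the 2–99 range point the same way. The article also condenses a fuller protocol, and it says that standard operating procedures guide the fieldwork.

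Much of this stands. The narrower meaning is probably what the authors intended, and the text does not show that they meant to leave adolescents untreated. It does not dispose of the point, because this is not a detail left to another document. The article states the rule twice, without a school level, and the rule conflicts with its own age range. A CHV who asks at the door whether a 16-year-old is in school would pass over a secondary pupil.

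A reader might infer more than the documents support:
- **A fault in all three groups.** In the control group, not treating secondary pupils is the intended comparator.
- **A need to catch up enrolled children who miss deworming day.** The 80% school coverage in the model already allows for children missed there.
- **Double dosing of non-enrolled children who attend school deworming.** This is speculative: teachers and CHVs both keep full treatment records.
- **An unresolved 6-month round for primary pupils.** Figure 1 is not shown and may settle it. The article also explains the absence of a biannual school group: "Mathematical models suggest that there is little difference in the impact of annual or biannual school-based deworming", given the expected prevalence.
- **A quantified loss of power.** That would need the predicted difference, which is not shown, and an assumption that secondary pupils gain nothing from reduced transmission around them. The article also describes 40 clusters as conservative.

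**Conclusion.** The point holds as a minor inconsistency in a stated eligibility rule, confined to the two community groups. Followed literally, it leaves secondary pupils without a scheduled mass-treatment dose and shrinks the treatment contrast modestly. The direction is towards a smaller difference from control, since these pupils are untreated there too.

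The loss is 0.70 percentage points of resident coverage for each 1% of residents in secondary school, or about 2–6 points if the share is 3–8%. That range rests on the assumed share, on 70% uptake among those newly eligible, and on CHVs applying the wording as it stands. If field practice already treats secondary pupils, the coverage loss is nil and only the text is wrong. Randomisation, the analysis and the validity of the comparison are unaffected.

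**What to change.** In both community-group definitions under Overall study design, replace *not enrolled in school* with *not enrolled in a primary school or early childhood development centre covered by the school programme*. Secondary pupils are then eligible for CHV treatment, and the two channels together match the stated age range. The sponsor should confirm that CHV instructions use the same wording.

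The cost is one phrase in each definition, one line in CHV training and, under the 3–8% assumption, about 105–280 extra albendazole doses per community unit per community round. The biannual group has two such rounds a year. No change to the design, sample size or analysis is needed.

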**Figure 1 BMJOPEN2015008950F1:**
[figure not shown]
Summary of study design.

### Interventions

All study groups will receive treatment with albendazole (400 mg), which is highly efficacious against *A. lumbricoides* and hookworm, but has lower efficacy against *T. trichiura.*^19^ What differs between the three study groups is the age range of populations that receive treatment and the frequency at which treatment is provided.

School-based deworming will be implemented in all communities as part of the national school-based deworming programme (NSBDP). Launched jointly in 2009 by the Ministry of Education, Science and Technology (MoEST), and the Ministry of Health (MoH), and funded by the Children's Investment Fund Foundation, the programme's goal is to eliminate STHs and schistosomiasis as a national public health problem. A single 400 mg dose of albendazole is provided annually by trained teachers on designated deworming days. The programme targets all children in at-risk subcounties enrolled in public and private primary schools and early childhood development centres (kindergartens).^20^ Non-enrolled school-age children are also encouraged to come to school for treatment on deworming day. The NSBDP makes use of a cascade model whereby trainings, materials, drugs and funds are channelled from the national level through the county to the school level, involving officials from MoEST and MoH throughout the cascade. The emphasis is on MoEST for delivery and MoH for supervision. Treatment coverage data and remaining drugs are returned along the reverse cascade. No adaptations shall be made to the NSBDP for the study other than modification of the treatment and coverage forms to strengthen the data capture on treatment at the individual level, and to validate treatment coverage.

Community-based deworming will be provided by CHWs, called CHVs in Kenya. CHVs already promote care seeking and compliance to antiretroviral and tuberculosis treatment, and mobilise populations during national health campaigns, as part of the national community health strategy.^21^ This strategy also includes the establishment of CUs, which each serve approximately 1000 households or 5000 people, with a single CHV providing service to approximately 100 households. For every 25 CHVs, there is one Community Health Extension Worker (CHEW) who is a Ministry of Health employee with training in public health or nursing. This CHEW provides supervision and technical support to the CHVs. The community health strategy was revised in 2010, with new guidance on the contents of CHV kits to include basic drugs such as paracetamol, albendazole and tetracycline.^22^ The community-based deworming in the present trials will provide door-to-door treatment, drawing on the previous experience of the National Programme for Elimination of LF, which, to date, has implemented four rounds of mass treatment (2002, 2005, 2008 and 2011), but with variable levels of treatment coverage.^23^

